## Abstract

**Introduction:**

While total hip replacement (THR) and total knee replacement (TKR) successfully reduce pain associated with chronic joint pathology, this infrequently translates into increased physical activity. This is a challenge given that over 50% of individuals who undergo these operations are physically inactive and have medical comorbidities such as hypertension, heart disease, diabetes and depression. The impact of these diseases can be reduced with physical activity. This trial aims to investigate the effectiveness of a behaviour change physiotherapy intervention to increase physical activity compared with usual rehabilitation after THR or TKR.

**Methods and analysis:**

The PEP-TALK trial is a multicentre, open-labelled, pragmatic randomised controlled trial. 260 adults who are scheduled to undergo a primary unilateral THR or TKR and are moderately inactive or inactive, with comorbidities, will be recruited across eight sites in England. They will be randomised post-surgery, prior to hospital discharge, to either six, 30 min weekly group-based exercise sessions (control), or the same six weekly, group-based, exercise sessions each preceded by a 30 min cognitive behaviour approach discussion group. Participants will be followed-up to 12 months by postal questionnaire. The primary outcome is the University of California, Los Angeles (UCLA) Physical Activity Score at 12 months. Secondary outcomes include: physical function, disability, health-related quality of life, kinesiophobia, perceived pain, self-efficacy and health resource utilisation.

**Ethics and dissemination:**

Research ethics committee approval was granted by the NRES Committee South Central (Oxford B - 18/SC/0423). Dissemination of results will be through peer-reviewed, scientific journals and conference presentations.

**Trial registration number:**

ISRCTN29770908.

Strengths and limitations of this studyThe effectiveness of a behaviour change physiotherapy intervention to increase physical activity compared with usual rehabilitation after total
hip replacement or total knee replacement will be demonstrated with a pragmatic clinical trial design.Functional, behavioural and psychological outcomes will provide evidence to determine the mechanisms by which the intervention is or is not effective.A multicentre recruitment approach will provide greater external validity across population characteristics in England.It is not possible to blind participants to the rehabilitation treatments given the participatory nature of the interventions.The group-based intervention may be challenging to ensure sufficient numbers within each group as participants enter the trial.

## Introduction

Total hipreplacement (THR) and total knee replacement (TKR) are the two highly successful orthopaedic procedures which reduce pain for people with osteoarthritis.^1 2^ Over 206 000 THR and TKRs were performed in UK in 2018.^1^ Approximately 90% of patients are satisfied following THR and TKR,^2^ with significant improvements in pain and physical function after 3 to 12 months.^2 3^

Historically, it has been assumed that people become more active following THR or TKR through the amelioration of joint pain.^4^ However, the current literature suggests physical activity, at best, remains the same from preoperatively to postoperatively and in some instances declines.^4 5^

People following THR and TKR have reported a number of challenges which make them engaging in physical activity difficult, most notably psychosocial barriers and fear of avoidance beliefs.^6^ Such barriers include receiving insufficient and inconsistent information on being more physically active, fear of damaging joint replacements and causing pain and not being able to goal-set or problem-solve physical activities within individual’s lifestyles.^6^ While previous international guidance has acknowledged the importance of physical activity on health and well-being, people following THR and TKR have acknowledged these difficulties in being more active.^6^ They have cited limited support or guidance currently offered on how to overcome these problems postoperatively.^6^

Not being physically active after joint replacement can have a major negative impact on a person’s health and a burden on the National Health Service (NHS). Medical comorbidities are common in this population. These include hypertension (56%),^7^ cardiovascular disease (20%),^8^ diabetes (16%)^8^ and multi-joint pain (57%).^7^ Twenty-seven per cent of people who undergo joint replacement have three to four comorbidities.^8^ Medical comorbidities have a significant negative impact on both health-related quality of life (HRQoL) and result in a societal burden.^9 10^ Participating in regular physical activity can decrease the risk of cardiovascular disease by 52%,^11^ diabetes by 65%^12^ and some cancers by 40%.^13^ It is associated with a reduction in all-cause mortality by 33% and cardiovascular mortality by 35%.^14^

Current rehabilitation following THR and TKR in the UK, as advocated by the British Orthopaedic Association, centres around regaining joint movement, strength and gait (walking pattern) re-education.^15^ There is currently no evidence informing patients or healthcare professionals on how to increase physical activity following THR and TKR. Previous research has demonstrated that behaviour-change interventions can effectively increase physical activity across the lifespan.^16–18^ However, following joint replacement, people have specific psychological needs and challenges which differ to the non-joint replacement population.^6^ Therefore, a specific intervention tailored to this population's health beliefs, including fear avoidance regarding implant survival, dislocation and increased knowledge on the impact of physical inactivity on other comorbidities, is required. Accordingly, the purpose of this trial is to answer the research question ‘following a primary THR or TKR, does a group exercise and behaviour-change intervention targeted to increase physical activity participation increase HRQoL and clinical outcomes over the initial 12 postoperative month compared with group exercise alone?’

## Methods and analysis

### Trial design

This is a two-arm, pragmatic, parallel, multicentre, randomised controlled superiority trial (RCT) to assess the effectiveness of a group exercise and behaviour-change intervention aimed to increase physical activity in people following THR or TKR. Nine UK NHS hospitals are involved in the trial across England. The study flow chart is presented as figure 1. Table 1 presents a summary of trial objectives, outcome measures and time points.

**Figure 1 F1:**
[figure not shown]
Study flow chart. THR, total hip replacement; TKR,
total knee replacement.

**Table 1 T1:** PEP-TALK trial objectives, outcome measures and measurement time points

Objectives	Outcome measures	Time points
**Primary objective**		
To compare physical activity participation at 12 months post randomisation between people who receive a group exercise and behaviour change intervention versus group exercise alone following THR or TKR.	University of California, Los Angeles Activity Scale	Baseline; 6 months; 12 months (primary time point)
**Secondary objectives**		
To compare the functional outcome between people who receive a group exercise and behaviour-change intervention versus group exercise alone following THR or TKR.	Lower Extremity Functional Scale	Baseline; 6 months; 12 months
To compare the disease-specific pain and function between people who receive a group exercise and behaviour-change intervention versus group exercise alone following THR or TKR.	Oxford Hip Score^36^ or Oxford Knee Score	Baseline; 6 months; 12 months
To compare the perceived level of pain between people who receive a group exercise and behaviour-change intervention versus group exercise alone following THR or TKR.	Numerical Rating Scale for Pain	Baseline; 6 months; 12 months
To compare participant’s self-efficacy between those who receive a group exercise and behaviour-change intervention versus group exercise alone following THR or TKR.	Generalised Self-Efficacy Scale	Baseline; 6 months; 12 months
To compare participant’s fear avoidance to movement between those who receive a group exercise and behaviour-change intervention versus group exercise alone following THR or TKR.	The Tampa Scale for Kinesiophobia	Baseline; 6 months; 12 months
To compare participant’s psychological distress (anxiety and depression) between those who receive a group exercise and behaviour-change intervention versus group exercise alone following THR or TKR.	Hospital Anxiety and Depression Scale	Baseline; 6 months; 12 months
To compare participant’s complications and adverse events between those who receive a group exercise and behaviour-change intervention versus group exercise alone following THR or TKR.	Complications or adverse events recorded in the case report forms	6 months; 12 months
To collect cost-effectiveness data (health resource utilisation; direct and indirect costs) of a group exercise and a behaviour-change intervention versus group exercise alone following THR or TKR.	EQ-5D-5L; Bespoke healthcare resource self-reported questionnaire	6 months; 12 months

### Trial participants

A minimum of 260 participants will be recruited.

Participants are eligible if they are:

Due to undergo primary (first time) unilateral THR or TKR where the indication for surgery is degenerative joint pathology (not trauma).Aged 18 years and over.Classified as ‘moderately inactive’ or ‘inactive’ using the General Practice Physical Activity Questionnaire (GPPAQ).^19^
Have a Charlson Comorbidity Index (CCI) of ≥1 point.^20 21^

Participants are ineligible if they have:

An absolute contraindication to exercise such as severe cardiovascular or pulmonary disease.Cognitive impairment defined as an Abbreviated Mental Test Score (AMTS)^22^ of <8.A usual place of residence that is a care home.Already enrolled onto another trial investigating physical activity, exercise adherence or behavioural therapy interventions.An inability to read and/or comprehend English.No access to a working telephone.

### Recruitment

Potential participants will be identified from UK NHS hospital trusts by the clinical team once they have been listed for THR or TKR. They will be asked whether they would like to know more about the PEP-TALK trial. There are two options for this: either they will be given a copy of the Participant Information Sheet (PIS) and asked to contact a member of the Clinical Research Network (CRN) research team who will provide more information or will be asked whether they are happy for a member of the CRN research team to contact them directly with more information about the trial. Verbal consent for the approach will be documented by a clinical team member in the medical notes.

Potential participants will be asked to read the PIS and asked to discuss their potential participation with anyone who they feel would provide useful advice such as friends, family member or carers. The number of people provided with the PIS will be recorded to monitor how many participants are assessed for initial eligibility and sent the PIS.

Eligible patients who agree to participate will provide their consent during the preoperative assessment appointment. Participant’s eligibility will then be verified by reviewing the medical notes and by interviewing the participant using the screening log, CCI and GPPAQ tools.

Written informed consent (online supplementary file 1) will be obtained prior to any trial-specific procedures being performed. The baseline case report form (CRF) will be completed at the preoperative assessments once consent has been taken. After the TKR or THR, eligibility will be confirmed by the site research team member reviewing the postoperative notes.

10.1136/bmjopen-2019-035014.supp1Supplementary data

### Randomisation, blinding and allocation concealment

Consented participants will be randomised (1:1) to the group exercise and behaviour-change intervention (intervention group) or group exercise alone intervention (control group) using the centralised computer randomisation service RRAMP (https://rramp.octru.ox.ac.uk) provided by the Oxford Clinical Trials Research Unit (OCTRU). This will either be undertaken directly by the site’s research facilitator or by contacting the trial office over the telephone, who will access the system on their behalf. Randomisation will be undertaken using a minimisation algorithm to ensure balanced allocation of participants across the two treatment groups, stratified by:

Hospital site.Type of joint replacement (THR or TKR).CCI of 1 to 3 versus ≥4.^20 21^

The minimisation algorithm will be seeded using simple randomisation and will have a probabilistic element introduced to ensure unpredictability of treatment assignment.

Baseline data will be collected during the preoperative assessment appointment and prior to randomisation. Therefore, the central randomisation system will issue a screening identifier (ID). Once the participant has been randomised, the central randomisation system will provide a participant ID to be used on all subsequent data collection forms. Sites will be responsible for linking the screening ID to the participant ID, with all linking information remaining at sites. This will be double-checked across the CRFs to ensure that the correct paperwork has been provided to the correct participant.

Due to the nature of the intervention, participants and those delivering the rehabilitation will be aware of the treatment allocation. By virtue of this design, it is not possible to blind participants, physiotherapists or the site researchers.

*Change to the randomisation allocation*: An amendment was made to the randomisation ratio in the minimisation algorithm from 1:1 to 2:1 (Experimental Intervention:Usual Care) after 75 participants had been randomised. The expected allocation ratio at the end of the trial is likely to be approximately 1.5:1. This was done to ensure that a greater number of people are allocated to the experimental intervention, which is a group-based intervention. As the experimental intervention was designed to have three or more people per group, early sites have found it difficult to consistently reach this level of participant numbers with the original 1:1 randomisation allocation. This change was made to reduce the risk of small numbers in the experimental group. The Trial Management Group (TMG) agreed this on 15^th^ August 2019. The sample size was increased to 260 to account for this change. This was approved by the sponsor, Data and Safety Monitoring Committee (DSMC) and research ethics committee.

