### Data analysis

#### Sample size

Originally, 250 participants (125 per arm) are required to detect a standardised effect size of 0.4 with 80% power and 5% (two-sided) significance, and allowing for 20% loss to follow-up. These calculations are based on the primary outcome, UCLA Activity Scale, at 12 months, assuming a baseline SD of 2.5 and a between-group difference of 1.^33^ The minimally clinically important difference has been reported as a within person difference of 0.92 points.^33^

The sample size was increased to 260 to account for the amendment in randomisation procedure from 1:1 to 2:1 group allocation, as described earlier.

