#### Statistical analysis

A detailed statistical analysis plan (SAP) will be drafted early in the trial and will be finalised prior to any primary outcome analysis. This will be reviewed and will receive input from the Trial Steering Committee (TSC) and the DSMC.

All analyses will be undertaken on the intent-to-treat population, that is, patients will be analysed as they were randomised regardless of the treatment received. Sensitivity analyses will be undertaken on the per-protocol population to assess a range of potential biasses that could have resulted from loss to follow-up, protocol deviations and withdrawal (including mortality). Numerical and graphical summaries of all data will be presented including descriptions of missing data at each level.

Estimates of treatment effects will be reported with 95% CIs. The primary outcome measure, UCLA Activity Scale at 12 months post-randomisation, will be analysed using a mixed effects linear regression model adjusted for baseline activity, 6 month time point and the stratification factors. Centre will be included as a random-effect to take account of their potential heterogeneity and type of operation, comorbidity index and other time points (baseline and 6 months) will be included as fixed-effects. Treatment by 6 month time point interaction will also be included in the model to allow time specific treatment effects to be calculated The adjusted difference in the means with corresponding 95% CI will be reported together with the mean and 95% CIs for each treatment group. If not normally distributed, then transformation to normality will be considered. If this is not possible, non-parametric techniques (for example Mann-Whitney or Kruskal-Wallis test) will be used with no adjustment. Consistency of any observed intervention effect will be explored using forest plots for various subgroups including site, type of operation (TKR and THR) and comorbidity index using interactions. No formal testing of interaction effects will be undertaken as the trial is not powered to detect these and the effect of the intervention is expected to be similar in the THR and TKR subgroups, although their baseline physical activity may be different, which will be taken into account in the analysis.

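### The allocation ratio changed after 75 of 260 participants, but the stated primary model has no term for allocation phase: a small risk of bias that one covariate removes

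*Protocol article*

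**What the plan says.** In the protocol article, under Randomisation, blinding and allocation concealment, participants are allocated by minimisation on hospital site, joint type and comorbidity band. The paragraph on the change to the allocation says that the ratio moved "from 1:1 to 2:1 (Experimental Intervention:Usual Care) after 75 participants had been randomised", because early sites had trouble filling intervention groups. It adds: "The expected allocation ratio at the end of the trial is likely to be approximately 1.5:1".

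The Sample size section carries the amendment into the numbers: "The sample size was increased to 260 to account for the amendment in randomisation procedure from 1:1 to 2:1 group allocation".

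The Statistical analysis section names the terms of the primary model. It is a mixed linear model adjusted for baseline activity, the 6-month time point and the stratification factors, with a treatment by 6-month interaction. Centre is a random effect, and "type of operation, comorbidity index and other time points (baseline and 6 months) will be included as fixed-effects". If normality cannot be reached by transformation, the plan moves to rank tests without adjustment. Neither allocation phase nor calendar time appears in the list, and no analysis by phase is mentioned.

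**The concern.** The chance of receiving the intervention was 1/2 for the first 75 participants and 2/3 for the rest. Within each phase the arms are comparable by randomisation. Pooled, they differ in when participants joined: the intervention arm holds relatively more late recruits. If 12-month activity differs between early and late recruits for reasons unrelated to treatment, part of that difference enters the treatment contrast.

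The model adjusts for the factors that steered the minimisation, but not for the one variable that changed the allocation probability. The amendment was followed through to the sample size, yet the article states no consequence for the analysis. At stake is a small bias in the primary estimate, of unknown sign, and a slight inflation of type I error.

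**Working it through.** **Inputs.** From Sample size: "detect a standardised effect size of 0.4 with 80% power and 5% (two-sided) significance", "assuming a baseline SD of 2.5 and a between-group difference of 1", "allowing for 20% loss to follow-up". From the allocation paragraph: 75 participants at 1:1, leaving 260 − 75 = 185 at 2:1. The size of any between-phase shift is not given; 0.5 to 1.0 point is an assumption, with 2 points as an extreme.

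**1. The plan's own sample size.** Evaluable N = (1 + k)(1 + 1/k) × [SD(1.960 + 0.842)/difference]², where k is the allocation ratio.
- k = 1: 196.2 in total. Rounded up to 99 per arm this is 198, and 198/0.8 = 247.5, so 248. The plan says "250 participants (125 per arm) are required"; 100 per arm divided by 0.8 gives exactly 125.
- k = 1.62 (step 2): 207.9/0.8 = 259.9, so 260.
- k = 1.5: 204.4/0.8 = 255.5.

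Both stated totals reproduce, and 260 fits the blended ratio.

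**2. Expected arm sizes.**

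| | Intervention | Control |
|---|---|---|
| First 75 (1:1) | 37.5 | 37.5 |
| Next 185 (2:1) | 123.3 | 61.7 |
| Total | 160.8 | 99.2 |
| Share after the switch | 123.3/160.8 = 76.7% | 61.7/99.2 = 62.2% |

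The overall ratio is 160.8/99.2 = 1.62, a little above the article's approximate 1.5. The gap in shares is 0.767 − 0.622 = 0.145.

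**3. Bias with no credit for baseline or centre.** Bias = 0.145 × shift. With 20% loss the arms are 128.7 and 79.3, and SE = 2.5 × √(1/128.7 + 1/79.3) = 0.357. Type I error = Φ(−1.96 + bias/SE) + Φ(−1.96 − bias/SE).

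| Assumed shift | Bias | Type I error |
|---|---|---|
| 0.5 | 0.07 | 5.5% |
| 1.0 | 0.145 | 6.9% |
| 2.0 | 0.29 | 12.8% |

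These are upper-end values. A shift of 1/0.145 = 6.9 points would be needed to create the whole 1-point target.

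**4. What centre adjustment leaves.** This needs a site-opening pattern, which the article does not give. Assume that all 75 early recruits, and half of the 185 later ones, come from sites open before the switch, and that the rest come from sites that opened later.
- Early sites: intervention 37.5 + 61.7 = 99.2; control 37.5 + 30.8 = 68.3. Gap in post-switch share = 61.7/99.2 − 30.8/68.3 = 0.171. Information = 99.2 × 68.3/167.5 = 40.5.
- Late sites: a single phase, so no gap. Information = 92.5 × (2/3)(1/3) = 20.6.
- Weighted: 0.171 × 40.5/(40.5 + 20.6) = 0.113 per point of shift.

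A simulation with five early and four late sites gave 0.055 and 0.114 for shifts of 0.5 and 1.0. At SE 0.357 these correspond to type I errors of about 5.3% and 6.2%. With 30% or 70% of later recruits at late sites, the same arithmetic gives 0.13 or 0.09 per point. Adjusting for site lowers the bias but does not remove it, because a site that recruits in both phases carries the imbalance within it.

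**5. With a phase term.** In a simulation with a 1-point shift and no true effect, mean bias was 0.13 without the term and −0.01 with it.

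**6. Price of the term.** Pooled information is 160.8 × 99.2/260 = 61.34. Within phases it is 75 × 1/4 + 185 × 2/9 = 59.86, which is 97.6% of the pooled value. With 20% loss, SE = 2.5/√(0.8 × 59.86) = 0.361 against 0.357, and power is 79.0% against 80.0%.

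**The case against.** The model already does much of the work. Baseline UCLA is the outcome measured before surgery, so case-mix drift visible at baseline is at least partly removed, and centre takes up stable differences between sites. This stands: the figures in step 3 overstate what the planned model would show, and step 4 still gives no credit for baseline. Neither adjustment reaches changes over time within a site that act after baseline.

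The shift is hypothetical. A 1-point shift equals the whole target difference and exceeds the 0.92-point within-person minimal difference that the article cites. This also stands.

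A reader might go further and infer that the treatment effect is confounded as a matter of fact, for instance through the season of the 12-month questionnaire or a different mix of sites. The document does not support that. It gives no shift, no site-opening dates and no date on which recruitment began. The mention of early sites says only which sites had trouble filling groups. Nor can the phases be split at 15 August 2019: that is when the Trial Management Group agreed the change. Sponsor, DSMC and ethics approval are also recorded, the current protocol version is dated 17 September 2019, and no implementation date is stated.

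Lastly, a covariate answering a mid-trial amendment could sit in the analysis plan, which is not shown and may contain it. Nothing in the article bars it. But the article does not leave the covariates open; it lists them, and the list omits phase.

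**Conclusion.** The point holds as a modest, removable risk. The ratio change and the missing term are both stated facts, and the 14.5 percentage-point imbalance follows from the article's own numbers, assuming that 260 are recruited at the stated ratios and that loss is equal in both arms and phases. The resulting bias is at most about 0.145 times any between-phase shift left after baseline and centre adjustment. For assumed shifts of 0.5 to 1.0 point this is at most 0.07 to 0.145 points, and about 0.055 to 0.114 with site adjustment under the assumed opening pattern. Against an SE of 0.36 it would rarely change the conclusion, and its sign is unknown. If the unadjusted rank tests were used instead, the protection from baseline and centre would be lost and the full imbalance would apply. The change is worth making because the trial's own amendment opened this path and closing it is cheap.

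**What to change.** Add allocation phase (randomised before or after the ratio change took effect) as a fixed effect in the primary and secondary models, and carry it in any imputation model. Take the cut from the randomisation record, that is, from when the 2:1 setting actually went live, and not from the date on which the change was agreed. Report the treatment effect by phase descriptively. If the rank-test fallback is kept, stratify it by phase. Fix all of this before the primary outcome is analysed.

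The cost is one binary variable that the randomisation record already supplies, about 2.4% of the information (SE 0.357 to 0.361), and about one percentage point of power (80% to 79%). The target of 260 need not change.
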